### Analysis Plan

#### Health Economic Data and Analysis

All resources required to measure the intervention implementation including the time spent by staff in training and on delivering the intervention will be monitored with site visits and allocated local collaborators at each site. The EQ-5D-Y will be used to measure health-related quality of life and its sensitivity will be explored. Considering this is a feasibility study, collected data such as intervention and resource-associated costs will be collected with relevant questions via qualitative interviews (eg, clinical opinion) to inform the economic evaluation for the future full-scale trial.

#### Quantitative Analysis

Demographic characteristics will be summarized using descriptive statistics. The between-cluster and within-cluster variance will be determined. Sample sizes for a future definitive trial will be based on detecting a difference in outcomes (mental health and risk presentation) between trial arms, estimated using the TROM and based on combinations of different alpha (ie, significance level) and beta (ie, power) rates. The ICC will be calculated using the linear mixed model and will explore correlations between participants within the same cluster, as well as to inform sample size calculation for the definitive trial.

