**Objective:**

This paper presents the protocol for a study that aims to test a feasibility cluster randomized controlled trial for young people transitioning from adolescent secure services to adult-oriented settings. The overarching aim of the MOVING FORWARD study is to provide a preliminary estimate of the effectiveness and cost-effectiveness of a new transition intervention model and to inform a future full-scale cluster randomized controlled trial.

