### Aims and Objectives

The MOVING FORWARD study aims to implement a new transition intervention model for young people transitioning from adolescent secure services to adult-oriented settings and test the feasibility of a future cluster trial measuring its effectiveness. The primary objectives are (1) to finalize the development of the intervention; (2) to determine the feasibility of conducting a full cRCT in adolescent secure inpatient units; (3) to test the feasibility and acceptability of trial procedures and materials, including recruitment, randomization, allocation, assessment tools, response rates, adherence and follow-up across 6 sites; (4) to determine the appropriateness of the proposed outcome measures; (5) to describe treatment as usual (controlled condition) across all sites; and (6) to qualitatively explore the views and experiences of health care staff delivering the intervention.

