### Allocation Strategy

The adolescent secure service is the unit of randomization and will be randomly selected until 6 sites are recruited. Sites were eligible if they provided low or medium secure care, or they were classified as PICUs. Six adolescent secure hospitals will be randomly allocated into 1 of 3 arms in a 1:1:1 ratio, stratified by area (south versus north) and type (medium versus low versus PICUs) first. Then participants at each site will be allocated to the same treatment. A total of 4 secure units will be allocated to the intervention arms and 2 units allocated to the control arm. Allocation will be performed (computer-generated allocation) by an independent member of the team who will be blind to the identity of the unit. Considering the nature of the intervention, young people and health care staff will not be blinded. The statistician and all team members collecting follow-up data, apart from the principal researcher and fieldworkers, will remain blind to the allocation of the units to trial arms.

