### Sample Size

An intraclass correlation (ICC) coefficient will be calculated to inform the power of the sample size for a further large-scale trial. A statistician based at the joint Faculty of Health, Social Care and Education at Kingston University and St George’s University of London will be involved in the design of the feasibility cRCT. This feasibility study aims to estimate the required sample size for a definitive cRCT evaluation of the intervention. We will estimate the variability in the likely definitive trial outcome (improved mental health and adjustment to adult settings upon follow-up) using an ICC. The sample size of young people may vary between 40 to 60 (8 to 10 young people at each site) and parents/carers 20 to 30 (4 to 5 parents/carers at each site) as recommended [20]. With a sample size of 50, we will be able to estimate a dropout rate of 80% (95% CI –11% to 11%).

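### The definitive trial is to be sized from a between-arm TROM difference and an ICC that six sites cannot estimate with usable precision, and the stated effectiveness aim matches none of the listed objectives

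*Protocol article*

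**What the plan says.** **Sizing the next trial.** Under Quantitative Analysis, sample sizes for the definitive trial "will be based on detecting a difference in outcomes (mental health and risk presentation) between trial arms, estimated using the TROM", over "combinations of different alpha (ie, significance level) and beta (ie, power) rates". The same section adds that "The ICC will be calculated using the linear mixed model". The Sample Size section says: "An intraclass correlation (ICC) coefficient will be calculated to inform the power of the sample size for a further large-scale trial".

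**Design.** Under Allocation Strategy, "Six adolescent secure hospitals will be randomly allocated into 1 of 3 arms in a 1:1:1 ratio", which is two sites per arm. It then says: "A total of 4 secure units will be allocated to the intervention arms and 2 units allocated to the control arm". The target is 50 young people. The TROM is listed for T1 and T2 only. The progression criteria ask for at least 70% follow-up at T1 and 60% at T2.

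**Aim.** The abstract's Objective states the overarching aim as "to provide a preliminary estimate of the effectiveness and cost-effectiveness of a new transition intervention model", together with informing a full-scale trial. The six primary objectives under Aims and Objectives are different in kind. One, for example, is "to determine the feasibility of conducting a full cRCT in adolescent secure inpatient units"; the others cover intervention development, trial procedures, outcome measures, usual care and staff views. None is an estimate of effectiveness or cost-effectiveness.

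The article gives no target TROM difference, SD, external ICC, or precision for the ICC or the arm difference. Its one precision figure concerns dropout.

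**The concern.** A sample-size calculation for a cluster trial depends mainly on the difference to be detected, the SD and the ICC. Alpha and power are conventions. The plan varies the conventions and, on its most natural reading, takes both the difference and the ICC from a study with two sites per arm. A chance large difference, or an ICC that happens to come out at zero, would make the next trial far too small. A chance small difference or a large ICC would make it look unaffordable. Informing that sample size is a stated purpose of the study, so the weakness touches something the study is for.

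The abstract's aim adds to this: it invites readers to treat an arm difference from this study as evidence about effect, although the objectives in the body do not ask for one.

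**Working it through.** **The plan's own figure.** For a rate of 80% with n = 50, the half-width is 1.96 × √(0.8 × 0.2/50) = 0.111, so the stated ±11 points reproduces. It treats the 50 as independent and says nothing about the ICC or the TROM difference.

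**Inputs from the article.** Six sites, two per arm. 50/6 = 8.33 young people per site; at 70% follow-up m = 5.83, at 60% m = 5. There is no baseline TROM to adjust for.

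**Assumptions (the article gives none).** ICC ρ = 0.05 unless varied, outcome SD = 1, equal site sizes.

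**1. Precision of the arm difference.** With k₁ and k₂ sites, SE = √{[ρ + (1 − ρ)/m] × (1/k₁ + 1/k₂)}.

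At T1, the first bracket is 0.05 + 0.95/5.83 = 0.213.
- 2 v 2 sites: SE = √(0.213 × 1) = 0.461. Half-width 1.96 × 0.461 = 0.90 SD, or 3.18 × 0.461 = 1.47 SD with t on 3 df.
- 4 v 2 sites, intervention arms pooled: SE = √(0.213 × 0.75) = 0.400. Half-width 0.78 SD, or 1.11 SD with t on 4 df.

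Sensitivity of the half-width, normal (t):

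| Setting | 2 v 2 sites | 4 v 2 sites |
|---|---|---|
| ICC 0, no loss | 0.68 (1.10) | 0.59 (0.83) |
| ICC 0.05, no loss | 0.79 (1.29) | 0.69 (0.97) |
| ICC 0.05, T1 at 70% | 0.90 (1.47) | 0.78 (1.11) |
| ICC 0.05, T2 at 60% | 0.96 (1.56) | 0.83 (1.18) |
| ICC 0.10, T2 at 60% | 1.04 (1.68) | 0.90 (1.27) |

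At T2 with ICC 0.05 (SE 0.49), the observed 2 v 2 difference has the wrong sign with probability Φ(−0.3/0.49) = 27% if the true effect is 0.3 SD, and Φ(−0.5/0.49) = 15% if it is 0.5 SD.

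**2. Precision of the ICC.** One-way F interval: F = 1 + mρ̂/(1 − ρ̂); F_U = F divided by the 2.5% quantile of F(df_b, 6(m − 1)); upper limit = (F_U − 1)/(F_U + m − 1). The between-site df are 5 if arm is ignored and 3 (six sites minus three arms) if arm is in the model.

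Example, ρ̂ = 0.05, m = 8.33, 3 df: F = 1.439; quantile 0.0713; F_U = 20.18; upper limit = 19.18/27.51 = 0.70. The lower limit is below zero and is set to 0 in every case.

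| m | Upper limit, 5 df | Upper limit, 3 df | P(estimate ≤ 0) if true ICC 0.05: 5 df / 3 df |
|---|---|---|---|
| 8.33 | 0.49 | 0.70 | 37% / 44% |
| 5.83 | 0.55 | 0.75 | 42% / 48% |
| 5 | 0.58 | 0.77 | 43% / 49% |

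**3. What this does to the next trial.** For a 0.5 SD target, 80% power and two-sided 5%, n per arm is 63 before clustering, multiplied by 1 + (8.33 − 1) × ICC.
- ICC 0: 63.
- ICC 0.49 (upper limit, arm ignored): 63 × 4.56 = about 288.
- ICC 0.70 (upper limit, arm-adjusted): 63 × 6.11 = about 385.

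That is a four- to six-fold span from ICC uncertainty alone. With the difference fixed in advance and the ICC varied over 0.01/0.05/0.10, n per arm is 68/87/110 for 0.5 SD and 188/240/304 for 0.3 SD.

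**The case against.** **The sentence may only name the endpoint.** Detecting a difference is ordinary sample-size language, and the sentence can be read as saying that the TROM will be the definitive outcome. The Sample Size section speaks of estimating variability in the likely outcome, which is a proper feasibility aim. Nowhere does the article say outright that the observed difference becomes the target. This stands as an ambiguity. Against it, the article refers to estimation with the TROM, offers no target difference, and varies only alpha and power. If the endpoint reading is meant, the text should say so and say where the target comes from.

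**The ICC is only to inform the sizing.** True: nothing says that it will be the sole input or used without an interval. But the one sensitivity dimension that the article names is alpha and power, not the ICC.

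**A reader might infer that the mixed model leaves arm out**, so that a real arm effect would inflate the ICC. The article does not support that. It lists no fixed effects at all, and model terms are normally left to the analysis plan. For the same reason the 3-df limits should not be quoted alone, as they presuppose an arm-adjusted model; both sets are given above.

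**A reader might infer that the design can provide none of these quantities.** That is too strong. Estimates can be computed, the aim is worded as preliminary, no progression criterion depends on effect, and no effectiveness test is stated.

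**The follow-up rates are minimum thresholds, and the main comparison may be 4 v 2.** Both fair. Full retention and pooling narrow the half-width to 0.69 SD at ICC 0.05, which is still too wide to set a target difference.

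**Conclusion.** The point holds as one of precision and wording, and should be fixed. Neither the arm difference nor the ICC from six sites is usable as a point value for sizing the definitive trial. At an assumed ICC of 0.05 and 70% follow-up, the difference carries a 95% half-width of about 0.90 SD (2 v 2) or 0.78 SD (4 v 2) on the normal approximation. An estimated ICC of 0.05 is compatible with anything from 0 to at least about 0.5. If the true ICC is 0.05, some 37–49% of such studies would return an estimate of zero or below.

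The conclusion on the difference does not hang on the assumed ICC: with ICC 0 and no loss, the half-widths are still 0.68 and 0.59 SD. The other assumptions are equal site sizes and a standardised outcome. Separately, the abstract's effectiveness and cost-effectiveness aim is not matched by any listed objective. This trial's conduct and its progression decision are not affected; what is at risk is the size of the next trial and how the arm differences are read.

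**What to change.** 1. **Quantitative Analysis, sizing sentence.** State that the definitive trial will be sized on a TROM difference fixed in advance as worthwhile, with stakeholder input, and not on the difference observed here. Take the SD, retention and cluster size from this study.
2. **Quantitative Analysis and Sample Size, ICC.** Report the ICC with its confidence interval, allowing for arm when it is estimated. Calculate the future sample size over a stated ICC range with external support (for example 0.01 to 0.10), as well as over alpha and power. The exact model specification can sit in the analysis plan.
3. **Abstract, Objective.** Drop or reword the effectiveness and cost-effectiveness estimate so that it agrees with Aims and Objectives, and say that arm differences will be reported descriptively with confidence intervals.

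The cost is wording and a small sensitivity grid; no sites, participants or data are added. The downside is a less ambitious stated aim and a range, not a single number, for the next trial's size.

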#### Qualitative Analysis

Recordings of interviews will be transcribed verbatim. Thematic analysis will be performed to identify key themes around transitions. The 6-step approach as suggested by Braun and Clarke [27] will be followed. Predetermined (derived from the literature) and data-driven codes will be used for transcription purposes. These codes will be refined to produce emergent themes. A constructionist approach will be followed to account for the impact of context and personal experiences. The transcripts will be examined for similarities, differences, and patterns. The experiences of young people will be explored to understand the intervention acceptability, implementation, and mechanisms of impact.

### Ethics

Approval by the Health Research Authority will be sought for the purposes of this research. The research team has extensive experience with submitting previous applications using the Integrated Research Application System to obtain ethical approval, including for vulnerable groups such as young offenders. Then, each site should provide an honorary contract or letter of access to the research team, facilitated by the Research and Development office at that site.

This protocol was submitted in January 2021 to the NIHR Advanced Fellowship Programme and has been internally and externally peer-reviewed by academic colleagues based at King’s College London and Kingston University.

## Results

### Important Themes Based on Advisory Group Feedback

The advisory groups highlighted themes of particular importance and relevance to the intervention, including communication and parallel care, transition delays, traumatic assessments, familiarity with adult services and key workers, and family engagement, and provided advice about the outcome measures. Young people described transition to adult services as scary, and they were keen to participate in the prospective feasibility study. A young person’s recommendation on providing peer support to improve self-management in the community was incorporated in the intervention. These areas have informed key aspects of the intervention, such as the inclusion of parents/carers, and its core modules, which improve the understanding and expectations of transitions and working with goals (described in more detail below and in Table 1).

### Timeline and Deliverables

The first year will be used for recruitment, finalizing the intervention, developing the protocol of the feasibility study, and training health care staff. During the second year, we will conduct follow-up assessments and data analysis. The final year will be used for report writing and dissemination of findings through patient and public involvement (PPI) and clinical collaborations to increase impact on policy transition guidelines and standard clinical practice. The deadlines outlined below will be followed strictly to manage the delivery of reports within the designated time frame. Study leaflets have been administered to potential participants already, and local collaborators have informed staff and young people about the feasibility study at all participating sites. Potential risks have been discussed with the advisory groups.

### Dissemination and Impact

Advisory group members, all of whom have direct or indirect experience of the transition from adolescent secure services to adult services, have expressed interest in providing PPI throughout the study to improve outcomes in design, data collection, analysis, and dissemination. One young person has been recruited as a member of the research team, and 2 parents and 2 young people have agreed to join the steering group, which will meet twice annually for 3 years. Additional PPI recruitment efforts are ongoing, aiming to recruit an additional young person and parent/carer to the steering group. A stakeholder group will be built including 1 NHS commissioner and 2 health care providers who have agreed to participate. The intervention will be finalized with the help of the steering and stakeholder groups, who will additionally review information sheets, consent forms, and outcome measures to check their appropriateness.

The findings are expected to be presented at national and international conferences, published in peer-reviewed journals, and communicated in regular study newsletters, meetings, and internal conferences at the participating sites. An internal networking event including adolescent and adult secure and community services will be organized to share the findings and receive input about the sustainability and inclusion of the proposed intervention in standard care. Kingston University in collaboration with the University of Warwick will hold a public dissemination event in which young people will reflect on their transition experiences. The findings will be also shared with NHS England and the Department of Health.

We will additionally work with young people who have returned to their communities, who will be supported to run local events in their catchment area to inform the public in accessible ways (using social media and YouTube) about transitioning to the community from secure care. Young people who have moved to adult secure hospitals will have an equal opportunity of being involved in the dissemination of the findings to their peers and their parents/carers by arranging internal community dissemination events in hospitals. A video will be created by young people who have moved to adult services to showcase to future cohorts.

### Progression Criteria and Feasibility Outcomes

A traffic light approach (stop-amend-go/red-amber-green) will be used and discussed a priori with PPI, advisory and local collaborators/key contacts, and research mentors about the following criteria:

Recruitment: at least 80% of targetIntervention fidelity: at least 80% of intervention workshops meet the fidelity criteriaIntervention acceptability: at least 80% of staff can be trained and deliver the intervention (barriers and facilitators to intervention design)Follow-up numbers: at least 70% at T1 and 60% at T2Acceptability of assessment tools: at least 70% at T1 and 60% at T2

The outputs are as follows:

Design a multicenter intervention for young people in transition;Design training manuals/toolkit for the health care staff involved in transition;Reflect on good practices across adolescent secure hospitals for transition to adult services and the community and management;Promote co-design and coproduction of evidence-based research.

The impact is as follows:

Design of the future cRCT will promote effectiveness and cost-effectiveness;Assess barriers and facilitators to providing the proposed intervention;Help services to reflect on quality of care and performance pre- and postdischarge;Enable young people to voice their experiences and be dynamically involved in their care.

Figure 3 presents the outcomes for the full-scale trial.

**Figure 3 figure3:**
[figure not shown]
Logic model: outcomes for the full-scale trial.

## Discussion

### Key Findings in Coproduction

This study aimed to describe the first and second stages of coproducing the MOVING FORWARD intervention. We collaborated with young people, parents/carers, and key workers from adolescent secure hospitals. In addition to addressing the gaps and concerns highlighted above, this research builds upon a previous NIHR Collaborations for Leadership in Applied Health Research and Care–funded PhD project titled *Transition of care in young offenders,* a multiphased study that illustrated the need for a national integrative care model that acknowledges the complexities involved in young people’s care journey. Factors found to impede effective transitions pertained to the severity of index offence, lack of parental involvement, disorganized service planning, and inconsistent clinical practice [20]. Groups at disadvantage were also highlighted, including young females with emerging borderline personality disorders and males with high-risk learning disabilities and long-term seclusion. Acknowledging the diversity in needs among young people has helped to coproduce and tailor the proposed intervention.

### Patient and Public Involvement

Young people and parents/carers are central to this study. Young people in secure care present with multiple comorbidities and challenging behavior, and do not have a dynamic role in decision-making as a result of being detained under the Mental Health Act legislation. Parents/carers are particularly concerned about transitions as they do not know what to expect and do not feel involved in the process. PPI will be sought at all stages of the study to improve outcomes in design, data collection, analysis, and dissemination. External PPI members will receive relevant training during the early stages of the study, and a point of contact from each site will be identified to ensure emotional support is provided in the event the young people feel distressed and direct them to appropriate services. A total of 5 young people and 5 parents/carers will be recruited to represent the study’s steering/PPI group and meet twice annually over the course of 4 years at St. George’s Hospital. One NHS commissioner and 2 health care providers will be involved in the steering groups.

Engagement of young people has been sought during the development of the intervention. The youth and parent/carer steering group will review information sheets, consent forms, and outcome measures to check their appropriateness. During the end of the study’s second and final year, young people from the advisory and steering groups will be asked to aid with the dissemination of the interim reports to their community and/or hospitals. The parent/carer advisory groups will be recruited from St Andrew’s and Cygnet’s Sheffield hospitals, and their views about the intervention model and how it can benefit young people will be collected. Feedback from all stakeholders will help to interpret the findings effectively and address how the intervention can fit future cohorts transitioning out adolescent secure services to facilitate the continuity of care.

